### Main effect of each of the CBT-components

To examine and compare the effectiveness of each of the distinct CBT-components (cognitive restructuring, behavioural activation, problem solving and relaxation), depressive symptoms at intermediate assessment 1 (*t*_*1*_) will be used as dependent variable to measure the effect directly after receiving the first module.

### Main effect of different sequencing

To investigate and compare the effectiveness of the four different sequences of CBT-components, depressive symptoms at post-assessment (*t*_*4*_) and 6-month follow-up (*t*_*5*_) will be used as dependent variables to measure the effect directly after treatment and six months after treatment. Marginal means will be computed under the linear mixed model and these will be used to graph the impact on depressive symptom levels when the CBT-components are being offered sequentially over time.

### Moderation

To explore effect moderation, baseline depression severity, comorbidity and the adolescents’ demographics will be used.

### Mediation

Mediation analyses will be performed to investigate whether negative cognitive errors, behavioral activation, problem solving skills and relaxation are mediators in the association between the type of CBT-component and depressive symptoms (at *t*_*1*_) and between the sequence of CBT-components and depressive symptoms (at *t*_*4*_ and *t*_*5*_).

### Cost-effectiveness of different sequencing

Cost-effectiveness analyses will be conduct in accordance with the CHEERS statement [78]. Cost data will be interpolated to a period of nine months under the assumption that data obtained with the cost diaries are representative for the periods in between. Binary logistic regression will be used to assess differences between the conditions in the percentage of adolescents below the percentile score of 76 based on the CDI-2 [50] norm scores (according to gender and age) and depression-free adolescents based on the K-SADS interview [55, 56]. In order to get insight in the uncertainty surrounding subtotal and total costs and due to highly skewed cost distributions, bootstrap simulations will be conducted. The bootstrap method estimates the sampling distribution of a statistic through a large number of simulations, based on re-sampling with replacement [79]. The results based on 1000 bootstrap replications of the costs of the four conditions will be used to calculate 95% confidence intervals (95% CI) around the cost-differences, based on the 2.5th and 97.5th percentiles. Bootstrap simulations will also conducted in order to quantify the uncertainty around the incremental cost-effectiveness ratio (ICER) [80], yielding information about the joint distribution of cost and effect differences. The bootstrapped cost-effectiveness ratios will be subsequently plotted in a cost-effectiveness plane, in which the vertical line reflects the difference in costs and the horizontal line reflects the difference in effectiveness. The choice of treatment depends on the maximum amount of money that society is prepared to pay for a gain in effectiveness, which is called the ceiling ratio. Therefore, the bootstrapped ICERs will be depicted in a cost-effectiveness acceptability curve showing the probability that a condition is cost-effective using a range of ceiling ratios. Also secondary (including QALYs based on the EQ-5D-Y) and sensitivity analyses will be performed to test the robustness of the results.

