### Sample size

The trial is well powered with *n* = 64 in each of the four conditions (*n* = 256 in total) to detect a clinically relevant effect (mean standardized difference, *d*) of *d* ≥ 0.33 as statistically significant (at α ≤ 0.05, 2-tailed) with a power of (1-β) ≥ 0.80 when the primary outcome (depressive symptoms) is evaluated in a baseline adjusted analysis of variance (ANCOVA) while also taking into account the nesting in the data owing to the cluster randomized trial.

More specifically, the power calculation was conducted using Stata’s 14.2 sample size procedure (*sampsi*) assuming that the evaluation would be carried out in a baseline adjusted ANCOVA with one baseline assessment and one follow-up (*t*_*1*_). The correlation (*r*) between *t*_*0*_ and *t*_*1*_ (*r* = .80) was estimated from preliminary data. This indicated that 52 respondents per condition were required. In a next step, we calculated the design effect of 1.22 while taking into account the intraclass correlation coefficient (*icc*), the mean cluster size (*m*), the coefficient of variation (*cv*) of the cluster sizes. The *icc* was estimated at 0.05, *m* and *cv* where estimated from preliminary data at 5 and 0.30, respectively. Hence, 64 (52*1.22) participants per condition are needed or a total *n* of 256. We will not increase the sample size at baseline to compensate for dropout, because all analyses will carried out in agreement with the intention-to-treat principle.

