### Data analysis

All analyses will be conducted according to the intention-to-treat principle (i.e., all participants, as randomised). Clustering of data will be taken into account, considering that small treatment groups of students (from the same school) will be randomized as a cluster to one of the four conditions. For all analyses multilevel mixed modelling in Stata [75] and Mplus [76] will be used. The four conditions will be included as fixed effects (i.e., by using dummy variables). For treatments groups random effects will be included [77]. Finally, the schools will be included by using fixed rather than random effects, because the between-school variability cannot be estimated well with the small number of available schools (we have included 11 schools so far). Possible baseline differences between the four conditions in depressive symptoms and demographic variables will be analysed. Variables that show differences between the four conditions will be entered as covariates in all models. When the data collection is complete, all members of the research team ([name]) will have access to the full dataset.

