The study also has limitations. We will not include a control group, limiting the extent to which a decrease in depressive symptoms in the four intervention groups can be uniquely ascribed to the prevention program. The reason for this is that several meta-analyses and reviews have already established the superior effect of CBT in comparison to waitlist and placebo (e.g., [81–83]). Another limitation is the design of a cluster randomized trial, because of the great risk on baseline imbalance between study arms [84]. We will try to reduce this risk by stratifying students by gender and age. The study’s power is also a limitation. Although the study is well powered on the main effects, the power might be too low for conducting moderation analyses. Therefore, these analyses will be done exploratory. At last, given previous prevention trials, we expect a high number of dropout in both the assessment and intervention phase, which will have consequences for the effectiveness [85]. In order to motivate adolescents to participate in the assessments, we will provide incentives for participation. Besides, all treatment drop-outs will be asked to complete the post- and 6-month follow-up assessments. To prevent the effect of dropout on the effectiveness, all analyses will be conducted according to the intention-to-treat principle.

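### Baseline utility, costs and K-SADS diagnosis are collected, but the economic comparisons specify no adjustment for them and the stated covariate rule leaves utility and costs out

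*Protocol article*

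**What the plan says.** Table 2 of the protocol article schedules the EQ-5D-Y, the parent cost diary and the K-SADS affective section at t0, t4 and t5. Each economic outcome therefore has its own baseline value.

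The section on cost-effectiveness of different sequencing describes the analysis in some detail:

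- **Binary effects:** "Binary logistic regression will be used to assess differences between the conditions in the percentage of adolescents below the percentile score of 76". The sentence goes on to include adolescents who are depression-free on the K-SADS.
- **Costs:** "The results based on 1000 bootstrap replications of the costs of the four conditions will be used to calculate 95% confidence intervals" around the cost differences.
- **Joint results:** bootstrapped cost-effectiveness ratios, a cost-effectiveness plane and acceptability curves.
- **QALYs:** mentioned once, as a secondary analysis based on the EQ-5D-Y, with no calculation method.

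No baseline covariate is named for any of these.

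The general rule is in the Data analysis section: "Possible baseline differences between the four conditions in depressive symptoms and demographic variables will be analysed". Variables that differ are then entered as covariates in all models. By contrast, the Sample size section does commit the primary outcome to a "baseline adjusted ANCOVA with one baseline assessment and one follow-up".

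**The concern.** A team following the text as written would examine baseline depressive symptoms and demographics, and would have no stated reason to look at baseline utility or baseline costs. K-SADS diagnosis is ambiguous: Table 2 lists depression diagnosis as a separate domain from depressive symptoms, so the rule reaches it only on a generous reading. For costs, the section describes a bootstrap of the four conditions' costs, not a model that a covariate could enter.

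This matters more here than in many trials, for three reasons.

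- All four conditions deliver the same four modules in a different order, so true differences in cost and QALYs are plausibly small.
- The randomised units are groups of about five, or roughly 13 per condition (64/5 = 12.8). Stratification covers gender and age only. The Strengths and limitations section names the cluster design as a limitation "because of the great risk on baseline imbalance between study arms".
- A depression diagnosis at entry is not among the exclusion criteria. Depression-free status at follow-up therefore combines students who were never diagnosed with students who recovered.

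The ranking of sequences on the cost-effectiveness plane and acceptability curves could then partly reflect who was healthier or cheaper at entry, and the estimates would be less precise than the collected data allow.

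**Working it through.** **The plan's own figures.** The inputs are in the Sample size section: d = 0.33, two-sided 0.05, power 0.80, r = 0.80 between t0 and t1, and "The *icc* was estimated at 0.05, *m* and *cv* where estimated from preliminary data at 5 and 0.30, respectively".

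- Per condition before clustering: 2 × ((1.960 + 0.842)/0.33)² × (1 − 0.80²) = 51.9, so 52.
- Design effect: 1 + ((0.30² + 1) × 5 − 1) × 0.05 = 1.2225.
- 52 × 1.22 = 63.4, so 64 per condition and 256 in total.

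The stated sample size reproduces. The protocol gives no corresponding figure for the economic analysis.

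**Size of chance baseline differences.** Assume the same ICC of 0.05 applies to the economic variables. Effective size is 64/1.2225 ≈ 52 per condition.

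- SE of a baseline difference between two conditions: SD × √(2 × 1.2225/64) = 0.195 SD.
- 95% range: ±1.96 × 0.195 = ±0.38 SD.
- K-SADS diagnosis: 1.96 × √(2p(1 − p) × 1.2225/64) gives ±8, ±11, ±15 and ±18 percentage points for an assumed baseline prevalence p of 5, 10, 20 and 30%.

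**Carry-over into QALYs.** Assume area under the curve by the trapezoid rule, with t4 at about 3 months (the nine-month horizon less the six-month follow-up). The weights on utility at 0, 3 and 9 months are 0.125, 0.375 and 0.25 years. With a common correlation r between assessments and no treatment effect, the expected QALY difference per unit of baseline utility difference is 0.125 + 0.625r: 0.31, 0.44 and 0.56 for r = 0.3, 0.5 and 0.7. For an assumed utility SD of 0.10–0.20:

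- One-SE imbalance: from 0.195 × 0.10 × 0.3125 = 0.006 to 0.195 × 0.20 × 0.5625 = 0.022 QALY.
- Imbalance at the 95% limit: 0.012 to 0.043 QALY.

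**Precision.** Under the same assumptions the correlation between the QALY and baseline utility is (0.125 + 0.625r)/√(0.21875 + 0.34375r). For costs, the correlation with baseline costs is taken as r itself. Adjustment multiplies the variance by one minus the squared correlation. Unadjusted power is taken at the effect for which the adjusted comparison has 80%, by normal approximation: Φ(2.802 × √(1 − corr²) − 1.960).

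| r | QALY–baseline correlation | QALY variance cut | Unadjusted power, QALY | Unadjusted power, costs |
|---|---|---|---|---|
| 0.3 | 0.55 | 30% | 65% | 76% |
| 0.5 | 0.70 | 49% | 52% | 68% |
| 0.7 | 0.83 | 69% | 35% | 52% |

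**Depression-free status.** Two-arm logistic regressions were simulated with 52 effective per arm, 10–40% diagnosed at t0, follow-up diagnosis of 60% in those diagnosed at t0 and 10% in the rest, and a log odds ratio of 1.2. Adding baseline diagnosis raised power by roughly 7 to 13 points when the effect raises diagnosis. The gain was roughly 1 to 11 points when the effect lowers it. All these inputs are assumptions.

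**The case against.** **Silence is not a decision.** The section nowhere says the comparisons are unadjusted, and a condensed article may leave economic covariates to an analysis plan that is not shown. This stands against a flat claim that the trial adjusts for none of these baselines. It does not remove the point, because the article does state a covariate rule, and that rule's scope omits utility and costs.

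**The general rule reaches all models.** Read literally, it includes the logistic regressions, so baseline CDI-2, and perhaps K-SADS status, can enter if conditions differ. A reader might infer that baseline diagnosis can never enter; the text does not support that. The quoted sentence on the 76th percentile is itself about a CDI-2 outcome, whose baseline counterpart the rule covers. The gap is firm for utility and costs and only arguable for diagnosis.

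**Randomisation protects the comparison.** A reader might also infer that baseline gaps pass straight into the results as bias. They do not. Over repeated randomisations they average out, and they are part of the variation that the bootstrap is meant to show. An unadjusted difference in depression-free proportions is a valid randomised contrast. Carry-over is partial, 0.31–0.56 per unit under the assumptions above. What remains is conditional imbalance in the one trial that is run, and lost precision.

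**The magnitudes are assumed.** The protocol gives no utility SD, correlations, diagnosis prevalence or QALY method. The ICC was set for planning depressive symptoms. The section itself calls costs highly skewed, so the normal approximation for cost power is rough. These objections stand, and the figures are illustrations.

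**Mitigation exists.** Stratification by gender and age, exclusion of students in current treatment for mood or anxiety problems, and promised sensitivity analyses all help, but none adjusts for baseline utility or costs.

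**Conclusion.** The point holds in a limited form. Three relevant baselines are collected, the economic section specifies adjustment for none of them, and the stated covariate rule excludes utility and costs by its scope and depends on observed differences for everything else. The firm quantity is that chance baseline differences between two conditions of up to about 0.38 SD lie within the 95% range; this uses the plan's sample size and design effect and assumes that the ICC carries over. The QALY shifts and power losses are conditional on assumed SDs, correlations, t4 timing and an area-under-the-curve method, and the K-SADS power gain is scenario-dependent. The consequence is avoidable imprecision and chance imbalance in the economic results, not systematic bias. The change is worth making because it uses data already scheduled and costs little.

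**What to change.** In the section on cost-effectiveness of different sequencing, specify the following regardless of observed baseline differences:

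1. Estimate QALY differences by regression of QALYs on condition and t0 EQ-5D-Y utility.
2. Estimate cost differences by regression of costs on condition and t0 cost-diary costs.
3. Include t0 K-SADS diagnosis in the depression-free logistic model, then convert the result to a standardised (marginal) difference in proportions. A conditional odds ratio cannot feed an ICER directly.
4. Compute these adjusted differences within each bootstrap replication and use them for the ICER, the plane and the acceptability curves. Keep the unadjusted results as a sensitivity analysis.

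If an analysis plan already does this, a sentence saying so is enough. The cost is wording and modest programming, with no new data. The small downside is that missing t0 utility or cost values need a simple baseline imputation so that those participants stay in the models.

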### Participants’ eligibility

Adolescents in all grades of secondary education (from pre-vocational education up to pre-university education) are eligible to participate in the study. Inclusion criteria for the adolescents are (1) aged between 10 and 20 years old, (2) sufficient knowledge of the Dutch language and (3) an elevated level of depressive symptoms at screening, defined as a percentile score of 76 or higher based on the Children’s Depression Inventory-2 (CDI-2; [50]) norm scores (according to gender and age). Exclusion criteria are (1) the absence of adolescents’ or parental consent (for subjects aged younger than 16), (2) currently receiving treatment for mood- or anxiety related problems and (3) suicidal ideation (expressed as a score of 2 (“I want to end my life”) on CDI-2 item 8 followed by a total score of 12 or higher on the suicide items of the Questionnaire assessing Suicide and Self Injury (in Dutch: Vragenlijst over Zelfdoding en Zelfbeschadiging; VOZZ, [51])). Adolescents who are identified with suicidal ideation (at any time point within the study), will be contacted within 48 h and referred to a general practitioner which in turn can refer to mental health care.

In order to minimize the number of false positives, an eligibility check will be conducted at baseline assessment (*t*_*0*_). However, adolescents who do not report an elevated level of depressive symptoms anymore (compared to screening) will not automatically excluded from the study, because of the episodic course of depression. In consultation with the adolescent it will be determined whether or not he/she will participate.

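### The cost-effectiveness comparison of students below CDI-2 percentile 76 reuses the entry cut-off without adjusting for the t0 score, so it is imprecise and its per-condition percentages are easy to misread

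*Protocol article*

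**What the plan says.** Under Participants' eligibility, entry requires "an elevated level of depressive symptoms at screening, defined as a percentile score of 76 or higher based on the Children’s Depression Inventory-2", on gender- and age-specific norms. The same section foresees screening errors: "In order to minimize the number of false positives, an eligibility check will be conducted at baseline assessment". That check is not an exclusion rule, because "adolescents who do not report an elevated level of depressive symptoms anymore (compared to screening) will not automatically excluded from the study"; participation is then settled with the student.

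Under Cost-effectiveness of different sequencing, binary logistic regression will assess "differences between the conditions in the percentage of adolescents below the percentile score of 76 based on the CDI-2", again on the gender- and age-specific norms. A second binary measure is "depression-free adolescents based on the K-SADS interview". The section then describes 1000 bootstrap replications, a cost-effectiveness plane and acceptability curves, and adds: "Also secondary (including QALYs based on the EQ-5D-Y) and sensitivity analyses will be performed to test the robustness of the results".

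The section names no baseline score for the percentile comparison. Under Data analysis, covariates enter the models only if they differ between conditions at baseline. By contrast, Sample size rests on a baseline-adjusted ANCOVA of the CDI-2 score.

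**The concern.** Being below percentile 76 later is the exact complement of the condition for entry. A student selected on one high screening score can cross back through measurement error and ordinary fluctuation alone. A student who has crossed back by t0 meets the measure before the first session and counts towards it by staying put.

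Two things are at stake:

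- **Interpretation.** There is no untreated arm, so a reported percentage below the line in any one condition has nothing to be set against, and part of it would be there without any program effect.
- **Precision.** The planned comparison reduces the CDI-2 to one crossing and ignores the t0 score, which predicts much of who will be below the line. The effect side of the incremental cost-effectiveness ratio is then less precise than the collected data allow.

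**Working it through.** **Inputs from the protocol.** Entry at percentile 76 or higher and outcome below percentile 76 (Participants' eligibility; Cost-effectiveness of different sequencing). From Sample size: d = 0.33, two-sided alpha 0.05, power 0.80, r = .80 between t0 and t1 from preliminary data, icc 0.05, mean cluster size 5, cv 0.30, 52 per condition before and 64 after clustering.

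**The plan's own figure.**
- ANCOVA: 2(1.96 + 0.84)²(1 − 0.80²)/0.33² = 51.9, so 52.
- Design effect: 1 + ((0.30² + 1) × 5 − 1) × 0.05 = 1.2225; 52 × 1.2225 = 63.6, so 64.
- Both reproduce. The effective number per condition used below is 64/1.22, about 52.

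**Share below the line with no effect.** The protocol gives no such rate, so this is a model: standard normal scores on the norm scale, correlation r between any two occasions, no change in mean. With X the screening score, Y a later score and c = 0.706 (76th percentile), the share is P(Y < c | X ≥ c) = 1 − P(X ≥ c, Y ≥ c)/0.24.

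| r | P(both at or above c) | Share below later |
|---|---|---|
| .93 | 0.193 | 19–20% |
| .90 | 0.184 | 23% |
| .80 | 0.161 | 33% |
| .70 | 0.143 | 40–41% |

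Putting the cut at the 75th percentile changes little (32% at r = .80). A right-skewed true score gives 19%, 28% and 35% for r = .9, .8 and .7.

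The row for r = .93 is there because the plan's .80 may come from students already selected for high scores. Selection narrows the range: a population correlation of about .93 gives about .79 between t0 and a later visit among the enrolled. In the other direction, .80 refers to t0–t1, and the correlation over the longer interval to t4 or t5 may be lower, which raises the share.

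**Already below at t0.** By simulation of screening, t0 and a later visit, of the students below the line later, about 55% (r = .93), 58% (r = .80) and 60% (r = .70) were also below it at t0. This assumes that every student below the line at t0 enrols.

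**Power for one pair of conditions.** Shift one arm by 0.33 SD of the enrolled sample. At r = .80 (cut at the 75th percentile) the percentage below the line moves from 32.4% to 45.5%. With n = 64/1.22 = 52.5 and mean proportion 0.390:
- numerator: 0.130 × √52.5 − 1.96 × √(2 × 0.390 × 0.610) = 0.944 − 1.352 = −0.408
- denominator: √(0.324 × 0.676 + 0.455 × 0.545) = 0.683
- power: Φ(−0.408/0.683) = Φ(−0.597), about 0.28

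Simulated power, 52 independent students per arm, for r between .80 and .93:

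| Comparison | Power |
|---|---|
| Below percentile 76, unadjusted, one visit | 0.27–0.30 |
| Below percentile 76, t0 CDI-2 as covariate | 0.32–0.42 |
| Below percentile 76 at both t4 and t5, unadjusted | 0.24–0.29 |
| CDI-2 score adjusted for t0 | 0.55–0.79 |

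The gain on the binary measure comes from the covariate. Requiring two visits lowers the no-effect share (33% to 19% at r = .80) but adds no power.

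**The case against.** A reader might infer that regression to the mean manufactures the effect in the economic analysis. The documents do not support that. The ratio uses differences between four randomised conditions, and regression to the mean is expected to be equal in all of them, so it contributes nothing in expectation to the contrast and does not inflate type I error.

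A reader might also infer that the plan labels these students as responders or as recovered, and so needs a minimum change or a confirming visit. It does not use those terms. It reports a status, and whether a student is still above the trial's at-risk line is a legitimate outcome in indicated prevention. Confirmation at t4 and t5 would not improve precision.

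Other points on the plan's side also stand. Strengths and limitations already discloses that the missing control group limits attribution. The CDI-2 at t4 and t5 is compared between sequences elsewhere in the plan. K-SADS status, QALYs and unspecified sensitivity analyses accompany the percentile measure. Acceptability curves are not significance tests, so power is only a proxy for precision here. Replacing the measure by cost per CDI-2 point would be a preference.

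What survives is narrower. None of these provisions brings the t0 score into the percentile comparison, and the general covariate rule does so only if the conditions happen to differ at baseline. Nor does any of them separate students who were below the line before session 1.

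**Conclusion.** The point holds as one of precision and presentation, not of bias. With no effect, about 20% to 33% of students would be below percentile 76 later (r about .93 to .80; about 40% at r = .70), and more than half of those would already be below it at t0. The percentage per condition should therefore not be presented as program benefit. The unadjusted comparison of two conditions has power of about 0.27 to 0.30 for d = 0.33, and adjusting for t0 gives about 0.32 to 0.42.

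These figures rest on normal scores, equal correlation between occasions, 52 effective students per arm in place of explicit clusters, no dropout, and enrolment of all students below the line at t0. If some of those students leave, the shares fall. The primary CDI-2 analysis is not affected.

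**What to change.** In Cost-effectiveness of different sequencing:

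1. Include the t0 CDI-2 score as a prespecified covariate in the percentile-76 logistic model, whether or not the conditions differ at baseline. Use the same adjusted effect difference in each bootstrap replication of the ICER.
2. Report the percentage below percentile 76 at t0 for each condition, and show students already below at t0 separately at later visits.
3. Optionally add cost per baseline-adjusted CDI-2 point as a sensitivity analysis (power 0.55 to 0.79). Its drawback is that it is harder to set against a ceiling ratio.

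A two-visit confirmation rule is not recommended. The cost is wording in the analysis plan plus one small table: the CDI-2 is already scheduled at t0, t4 and t5, and neither eligibility nor sample size changes.
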